## Discussion

The purpose is to show that optimized follow up of patients after a stroke involving nursing personnel assigned to the department and a family member/friend of the patient can, in association with the vascular neurologist and the attending physician, better control the risk factors and improve the prognosis in terms of morbidity/mortality. This will make it possible to validate and evaluate the advantage of greater involvement by nursing personnel specializing in vascular pathology in following up on patients who have had a stroke. This demonstration, based on a comparative, randomized study, will provide an answer with a greater level of proof than a simple observational study. On the medico-economic level, it will be possible to bring in objective elements to show that the cost invested in involving nursing personnel in post-stroke follow up can provide savings by reducing the costs related to post-stroke morbidity/mortality, while at the same time improving patients’ health and quality of life. In addition, performing this study will optimize the organization of the research network on nursing care in the Strokavenir network.

The involvement of both the dedicated nursing personnel and a designated member of the patient’s family circle is an original approach to optimized follow up of patients who have had a stroke. Although nursing personnel have already been involved in therapeutic educational action or follow up in a network of patients who have had a stroke, this is, as far as we know, the first actual comparative, multicenter study, which will give important solidity to the possible differences observed. On an international level, a comparative study is in progress in Canada but is based on follow up by a volunteer outside the family, and has no nurse involvement. A recent study involving nurses in multidomain vascular care to prevent dementia had negative results, but it was a study conducted in the general population while the CEOPS study will focus on a stroke patient population in which secondary prevention is crucial, with effectiveness already demonstrated.

The purpose of the study is to lower the morbidity/mortality, which may follow the onset of a first stroke, using optimized follow up. Considering the complexity of the morbidity/mortality criterion and the necessary feasibility criterion in terms of the number of subjects needed, the choice of the main assessment criterion, blood pressure, offers the dual advantage of being strongly correlated with risk in terms of morbidity/mortality and of being a relevant criterion in nursing care. Nevertheless, the results obtained in the Prediva study prompted us to consider a greater decrease in blood pressure as a primary endpoint, in the perspective of the impact on morbidity/mortality, but with reasonable objective since a too important blood pressure decrease is able to induce a deleterious effect. Parameters that are the domain of both medical and nursing care have been considered as secondary criteria. In the case of positive results, the CEOPS will constitute the basis of validated guidelines to optimize a multidomain intervention program for the follow up of patients after stroke, which is now a recommendation and a legal obligation in France. The preliminary descriptive analysis suggests a target population focused on younger patients with less severe stroke, which is the population needing optimal care to avoid recurrence and cognitive decline (Additional file 1).

### Trial status

Among the 410 planned patients, we have already recruited 215 patients. The first patients were included on 27 January 2014 in the Lille center. The 14 other centers activated recruitment between 14 November 2014 and 27 October 2016. The success and speed of trial implementation is resulting from the hospital organization, in particular nurse activities that remain heterogeneous between the different centers. The mean number of patients recruited per center is 14. We planned to achieve the recruitment target by June 2019.

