**Fig. 2 Fig2:**
[figure not shown]
Schedule of enrollment, interventions, and assessments

The study will be presented at the time of an interview with the nursing personnel from the department assigned to the CEOPS study, in the presence of the doctor from the department, and a family member/friend likely to participate in the optimized follow up will be identified. The family member/friend is chosen on a voluntary basis, on the ability to understand and follow the different aspects of the recommendations, and on the proximity to the patient. After a period of consideration, the patient and the caregiving family member/friend will give their consent to participate in the study. Patients will be randomized into two groups, “optimized follow up” or “typical follow up.” Before being discharged, the two training sessions for the patient and the caregiving family member/friend will be given by the nursing personnel assigned to the CEOPS study. A letter of information will be sent to the attending physician and, possibly, to the other specialist physicians involved in the patient’s management (cardiologist, diabetologist, etc.). Before being discharged, blood pressure, the abdominal perimeter, glycosylated hemoglobin, plasma concentrations of the various lipids, coagulation parameters, the Rankin score, the quality of life scale and the Montreal Cognitive Assessment (MoCA) scale will be measured. The treatment upon discharge will be assembled.

In both groups, the patient and the family member/friend involved in the CEOPS study will be asked to fill out a follow-up notebook, where the following are to be noted: monitoring of blood pressure and various examinations performed, all the para-clinical examinations and consultations the patient has had, the adverse effects observed and the inter-current events. At each consultation, a report will be sent to the attending physician to keep the physician informed of the conclusions of the medical consultation. The nursing personnel assigned to the CEOPS study can at any time call on the physician in the department handling the patient’s follow up to inform the attending physician of the need for a change in treatment if it is found that the risk factors are not being properly monitored. One last information session will provide encouragement to the family member/friend to continue to be involved in the patient’s follow up in order to continue optimal monitoring of the risk factors and the treatment.

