### Sample size consideration

A population of 410 patients (205 in each arm) will be included in the study. The number of subjects necessary was calculated to show a difference in systolic blood pressure of 5 mmHg between the group with optimized follow up and the group with typical follow up, with an alpha risk of 5% and a beta risk of 20%. The variance in systolic blood pressure (18 mmHg) was calculated in the first 45 patients included in the study, in whom mean systolic blood pressure was 139.9 mmHg. The choice of the expected difference was justified by three reasons. First, there is a link between increase in blood pressure and the risk of stroke. Second, the Prediva study showed recently that a 2-mmHg decrease in blood pressure was unable to impact cognitive morbidity in the general population [32]. Third, with a 5-mmHg decrease in blood pressure, mean blood pressure should reach 135 mmHg, a level that is recommended in the guidelines and is in good accordance with a previous study [28].

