### Analysis strategy

Data will be analyzed by an analysis committee that will be blind to the groups studied, which will be called Groups A and B during the analysis. The assessment criteria will be expressed as quantitative values (mean and standard deviation) or as qualitative values (percentage). The variables expressed quantitatively will be blood pressure (systolic, diastolic, mean), glycosylated hemoglobin concentration, concentration of the various lipid parameters and scores on different scales (Rankin, MoCA, EQ-5D). The variables expressed qualitatively will be mortality rate, percentage of patients having another stroke, percentage of patients having blood pressure below the limit set by international guidelines, percentage of patients with normal glycosylated hemoglobin, percentage of patients with LDL cholesterol below 1 g/L and percentage of patients having a cognitive disorder (MoCA score <26). Quantitative data will be compared between the two groups using analysis of variance, with post-hoc analysis using Fisher’s least significant difference test in Prism (PLSD). Qualitative data will be compared between the two groups based on the chi-squared test and calculation of odds ratios. Sub-group analyses will be planned secondarily, depending on the cause of the stroke or depending on the patient’s cognitive state.

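### The stated two-group ANOVA uses neither baseline systolic pressure nor centre, and makes no allowance for patients sharing a nurse in the optimized arm

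*Protocol article*

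**What the plan says.** Under Analysis strategy: "Quantitative data will be compared between the two groups using analysis of variance". A post-hoc test is named, but no covariate, centre term or nurse term. The main criterion (Primary outcome) is systolic pressure after one year.

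Under Sample size consideration: "A population of 410 patients (205 in each arm) will be included in the study", "calculated to show a difference in systolic blood pressure of 5 mmHg", with alpha 5% and beta 20%. The spread is given as follows: "The variance in systolic blood pressure (18 mmHg) was calculated in the first 45 patients included in the study". No ICC or design effect appears.

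The sections on the two follow-up procedures put the departmental study nurse's sessions, telephone calls and repeat training in the optimized arm. Follow up in the typical arm belongs to the attending physician alone. Procedure describes randomization of individual patients and lists blood pressure among the measurements taken before discharge.

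Trial status gives Lille plus 14 other centres, and "The mean number of patients recruited per center is 14". It also attributes the success and speed of implementation to hospital organization, "in particular nurse activities that remain heterogeneous between the different centers".

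**The concern.** Two separate things are left out of the named analysis.

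First, pre-discharge pressure and centre are both known for every patient and both are likely to explain part of the 12-month value. A plain two-group comparison leaves that variation in the residual. The cost is precision, not validity.

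Second, the design is partially nested: optimized-arm patients are grouped under study nurses and typical-arm patients are not. If some nurses achieve more than others, the outcomes of patients under the same nurse are correlated, and an ANOVA on independent patients ignores this. It matters because the Discussion wants a positive result to support guidelines on follow up after stroke. That is a statement about nurses in general, so its interval should carry nurse-to-nurse variation.

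**Working it through.** **Inputs from the article.** 205 per arm; difference 5 mmHg; alpha 5% (taken as two-sided); power 80%; spread 18 mmHg; 15 centres. At full recruitment 410/15 = 27.3 patients per centre and 205/15 = 13.7 optimized-arm patients per centre.

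**Assumptions, not in the documents.** One nurse cluster per centre; equal centres; complete 12-month data; nurse ICC of 0.01 to 0.05 in the optimized arm only.

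**1. The plan's own figure.** n per arm = 2 × (1.960 + 0.842)² × 18² / 5² = 204; the exact t-based calculation gives 205. The 18 mmHg, although called a variance, works only as a standard deviation (read as a variance it gives 12 per arm). Power at 205 per arm is 80.3%. The figure therefore reproduces, with patients taken as independent.

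**2. Standard error under independence.** 18 × √(2/205) = 1.778 mmHg.

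**3. Nurse clustering in the optimized arm.**
- Design effect in that arm: D = 1 + (13.67 − 1) × ICC
- True SE = 18 × √((1 + D)/205)
- Type I error of the plain ANOVA = 2 × [1 − Φ(1.96 × 1.778 / true SE)]
- Power of a correctly sized test = Φ(5 / true SE − 1.96)

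| Nurse ICC | Between-nurse SD (18√ICC) | D | True SE | Increase over 1.778 | ANOVA type I error | Power, correctly sized test |
|---|---|---|---|---|---|---|
| 0 | 0 | 1.000 | 1.778 | 0% | 5.0% | 80.3% |
| 0.01 | 1.8 mmHg | 1.127 | 1.833 | 3.1% | 5.7% | 77.9% |
| 0.02 | 2.5 mmHg | 1.253 | 1.887 | 6.1% | 6.5% | 75.5% |
| 0.05 | 4.0 mmHg | 1.633 | 2.040 | 14.7% | 8.8% | 68.8% |

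These use the normal approximation; small-sample degrees of freedom would lower the power a little further.

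**4. Centre differences shared by both arms.** Let C be the share of variance due to centre level and N the nurse share. With arms balanced within centre, the true variance of the difference is 324 × [(1 − C)/205 + (1 − C − N)/205 + N/15].
- C = 0.05, N = 0: SE 1.733, ANOVA type I error 4.4%.
- C = 0.10, N = 0: SE 1.687, ANOVA type I error 3.9%.
- C = 0.10, N = 0.01: SE 1.745, still 1.9% below 1.778.
- C = 0.05, N = 0.05: SE 2.001, 12.5% above 1.778.

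If randomization is not balanced by centre (the article does not say), a simulation of 6,000 trials with C = 0.05 and N = 0 gave an empirical SE of 1.774 against a mean ANOVA SE of 1.775, with type I error 4.8%. Shared centre differences thus leave the ANOVA about right or conservative. Only the nurse (or arm-by-centre) component makes its SE too small.

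**5. Precision from baseline.** Adjusting for a baseline value with correlation r to the 12-month value multiplies the residual variance by about 1 − r². The article gives no r, so the gain is not quantified here.

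**The case against.** A reader might infer that, because the centres are unlike, the ANOVA standard error is certainly too small. The documents do not support that. Patients are individually randomized, and step 4 shows that differences in level common to both arms do not shrink the standard error. The direction depends on a nurse variance that the article does not give.

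A reader might also take the Trial status remark on nurse activities as proof that the intervention works differently by centre. Its subject is how well and how fast the trial was set up. Other sections point towards standardization: nurses informed about common education guidelines, one brochure, a programme of sessions and calls laid down for all centres, and treatment changes made by physicians. The remark should carry no weight here.

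Three further objections stand in part.
- If the programme has no effect with any nurse, there is no nurse-effect variance and no inflation. The type I figures describe nurse effects that vary around a zero mean.
- For the average effect among the participating nurses only, the between-nurse component need not enter the standard error. That target is legitimate, but it is narrower than the guideline use that the Discussion foresees.
- The number of nurses per centre is not stated. More than one per centre would reduce the inflation; unequal centre sizes would increase it.

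Finally, this is a condensed article and the SAP is not shown, so covariates and random effects may be specified there. Still, the article names a specific method, and its sample size matches independent patients. If the SAP already has these terms, the point is met.

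**Conclusion.** The point holds in conditional form. The named ANOVA gives up precision by using neither baseline systolic pressure nor centre. It also understates uncertainty if nurse effects vary and the conclusion is to extend beyond the nurses who took part.

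Under the stated assumptions the understatement is modest at the low end of the ICC range and material at the high end. The upper end needs a between-nurse SD of 4.0 mmHg, which is 80% of the 5 mmHg target (4.0/5), so it should be read as a bound on the range shown, not as an expectation. The case rests on who delivers the follow up in each arm, not on any evidence in the documents that effects differ between centres.

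**What to change.** **Primary model.** A linear model of 12-month systolic pressure on arm, baseline systolic pressure and centre. The SAP should name the baseline reading, preferably one taken before randomization: the article places a reading before discharge but does not order it against randomization or the first training session.

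**Sensitivity analysis.** Prespecify a model with a random nurse effect in the optimized arm (or a random arm-by-centre effect) and Kenward-Roger degrees of freedom. Cite its interval wherever the report generalizes to nurse-led programmes. The centre term in the primary model does not itself deal with nurse clustering, so this second model is needed for that purpose. State the ICC assumed, and confirm that nurse identity is recorded for each optimized-arm patient.

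**Cost.** SAP wording, with no change to randomization, visits or sample size; centre is known and pre-discharge pressure is already collected. The downside is a somewhat wider sensitivity interval if nurse effects are real.

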## Abbreviations

EQ-5D: EuroQoL 5-Dimension questionnaire
GP: General practitioner
HDL: High-density lipoprotein
LDL: low-density lipoprotein
MoCA: Montreal Cognitive Assessment
TOAST: Trial of Org 10172 in Acute Stroke Treatment
